#### Randomization

Following the baseline assessment, a research assistant uninvolved in the assessments or implementation of the study will use a computer-generated randomization list from www.random.org to randomly assign participants by gender to either the intervention (IG) or control group (CG). A research assistant will contact the dyads by telephone to inform them about their allocation and schedule a first home visit. It will not be possible to blind participants to their treatment allocation due to the nature of the intervention.

#### The individualized music and dementia app

All dyads will receive a tablet (Samsung Galaxy Tab A8) pre-installed with the self-developed Individualized Music and Dementia (IMuD) app. We designed the IMuD-App to be exceptionally user-friendly (e.g., large font, explanations in simple language, intuitive navigation). The IML intervention is delivered via the app. All caregivers will additionally use the app to complete and submit daily assessments as described below. Throughout the intervention, caregivers can also use the app to contact the research team using a contact form.

#### Intervention

After randomisation, the tablet will be sent to participants of the IG via mail. Caregivers in the IG will complete an assessment of music that is personally-relevant to the person with dementia. The assessment includes open question (e.g. “Which songs were heard at family celebrations?”), multiple-choice questions (e.g. regarding the preferred genre) and, based on a search of popular music from different decades, a list of examples of popular artists and song titles. To the extent possible, the assessment will be completed together with the person with dementia. The caregiver will submit the completed assessment via the app. Based on the completed assessment, the project team will create three individualized music playlists for each person with dementia in the IG.

People with dementia in the IG will then listen to their individualized playlists for 20 min every other day (3–4 times a week) for six weeks, through headphones if possible. Dyads can choose when the sessions take place and skip a session if necessary. The caregiver and/or person with dementia can freely choose one of the three music playlists which are stored on and played through the app. The caregiver will be supported to find out what accompaniment the person with dementia needs when listening to the music. Videos and written recommendations in the app provide guidance on how the caregiver can optimize the listening situation, interact with the person with dementia during the listening sessions, and respond to any challenging situations (e.g., lower the volume or change the song if the person with dementia becomes agitated).

Participants in the CG will receive no IML intervention and organize their everyday life as usual. Members of the CG will receive 200 Euro at the end of successful participation in the study. The renumeration is provided to the dyad as a unit. Dyads of the IG will receive no renumeration.

The project team will contact participants in both the IG and the CG regularly in order to encourage continued participation and address any arising problems.

#### Home visits

During the six-week intervention period, two project members will conduct a total of three home visits per dyad. The home visits will take place in the first, third or fourth (depending on the dyad’s availability) and sixth week of the intervention period. The dyads will receive informational brochures on dementia during each home visit.

During the first home visit, caregivers in the CG will receive the same tablet as caregivers in the IG. The project member will provide the caregiver with a detailed technical briefing of the app and an introduction to the daily assessments. Together with the project member, caregivers in the IG will additionally watch instructional videos via the app regarding how to conduct the music listening sessions.

The project member will then use the Mini-Mental-State-Examination (MMSE) [29] to assess the severity of dementia of the care recipient. If the MMSE score exceeds 10, the project member will use the Subjective Quality of Life Inventory [30] to assess the person with dementia’s ability to make statements about their own well-being.

During each home visit, a trained project member will use a revised version of the Dementia Coding System (DeCS) [17] to record the reactions and behaviours of the person with dementia. The coding system was adapted for the current project and includes 26 items covering the people with dementia’s emotional, physical, and communicative behaviour (e.g., facial expressions, gestures, body movement). A trained research assistant will use the DeCs to assess the behaviour of the person with dementia in 15 time-units of four minutes each (60 min in total). For participants in the IG, the project member will record the behaviour of the person with dementia 20 min before, 20 min during, and 20 min after the listening session. For participants in the CG, the project member will record the behaviour of the person with dementia during a 60-min open conversation.

Provided consent, the behavioural observations will be filmed. One camera will record the face of the caregiver, a second camera will record the face of the person with dementia, and a third camera will record a 360° view of the room. As described below, the videos will be analysed for indications of (acute) physiological stress, reactions to the music and dyadic interactions at a later time point.

Provided consent, the research team will additionally collect hair samples from the person with dementia and the caregiver during the first and third home visits. As described below, the hair samples will be analysed for indications of chronic physiological stress.

During the third home visit, a project member will conduct a semi-structured interview to capture participants’ experiences with the tablet, app, daily assessments, home visits and project team. Caregivers in the IG will also be asked to describe their perceptions of the feasibility, acceptance, applicability, and effects of the IML intervention. To the extent possible, the participants with dementia will be asked to describe their own experiences.

The research team will collect the tablets and further technology at the end of the third home visit.

#### App-based daily assessments

During the six-week intervention period, all caregivers will use the app to complete daily ecological momentary assessments of their own well-being and arousal, the well-being and arousal of the people with dementia and the caregiver-care recipient interaction. At a time of the caregivers’ choosing, the app will prompt the caregiver to complete the questionnaire with an audible beep. Caregivers can skip an assessment if they do not have time on a day.

#### Questionnaire assessments

In addition to the app-based daily assessments and the home visits, paper-and-pencil questionnaires will be sent to the participants by mail directly before the intervention (T1), directly after the intervention (T2), and six weeks later (T3). All questionnaire assessments are identical.

#### Adverse events

Caregivers will be supported to find out what accompaniment the person with dementia needs when listening to music. Caregivers should remain present during the first IML sessions to be able to intervene if necessary. To empower the caregivers, project members will personally provide a detailed introduction to the technology and the IML intervention. If the person with dementia repeatedly reacts negatively to the music, it is possible to change the song permanently, lower the volume, pause or stop the music. Participants can stop a listening session or drop out of the study at any time.

### Outcome measures

An overview of the assessments and outcome variables is provided in additional file 1.

#### Primary outcome: individual goal attainment

Standardized outcome measures may underestimate the effects of IML. We therefore focus on participants’ *individual goal attainment* after six weeks of IML or treatment as usual as the primary outcome. We will use the Goal Attainment Scaling (GAS) approach to assess individual goal attainment [31]. The extent to which the individual goals formulated during the T0 telephone interview were attained will be quantified using a 5-point scale (-2 = “severe deterioration”; + 2 = “complete goal attainment”; [32]).

#### Well-being of person with dementia: self and caregiver perceptions

Based on the circumplex model of emotion [33], caregivers will use visual analogue scales ranging from 0 to 100 [34] to assess the person with dementia’s *emotional well-being* and *arousal* daily via the app and as part of the paper-and-pencil questionnaires assessments at T0, T1, T2, and T3.

To the extent possible, participants with dementia will provide self-reports of their well-being and quality of life. During each of the three home visits, participants with dementia will use the Dementia Mood Picture Test [35] to self-assess their *emotional well-being* by selecting which of six faces (bad mood, angry, sad, worried, good mood, happy) best represents their emotional state. Participants with dementia will also use the Heidelberg Instrument for the Quality of Life of Dementia Patients [36] to indicate their *overall life satisfaction* (1 = “not at all satisfied” to 4 = “very satisfied”).

#### Behavioural and psychological symptoms of dementia

Caregivers will assess the person with dementia’s BPSD as part of the paper-and-pencil questionnaires assessments at T0, T1, T2, and T3. Caregivers will use the German-version of the Behavioural Pathology in Alzheimer’s Disease Rating Scale [25]. Caregivers use a dichotomous response scale (0 = “not present”, 1 = “present”) to indicate the extent to which the people with dementia displays each of 23 BPSD covering four factors (Paranoid and Aggressiveness, Hallucinations and Agitation, Affective Disturbances, Anxieties and Phobia). Caregivers will additionally use the Cornell Scale for Depression in Dementia [37] to assess the people with dementia’s *depressive symptoms*. Specifically, caregivers are asked to indicate the extent to which the person with dementia has each of 19 symptoms of depression using four answer categories (0 = “absent”, 1 = “mild/intermittent”, 2 = “severe”, 3 = “assessment not possible”). Caregivers will also use a visual analogue scale ranging from 0 to 100 to assess the people with dementia’s *resistance during care *[38].

During the home visits, a trained project member will also use the revised version of DeCS [17] to assess the person with dementia’s BPSD as part of the behavioural observations. A subset of 14 of the 26 behaviours assessed by the revised DeCS are BPSD (e.g., resistance/refusal behaviours).

#### Caregiver’s well-being

Caregivers will assess their *emotional well-being* and *arousal* daily via the app (daily assessments as well as directly before and after IML) and as part of the pencil-and-paper assessments at T0, T1, T2, and T3. Caregivers use visual analogue scales ranging from 0 to 100 [34].

#### The caregiving experience

Caregivers will assess the caregiving experience as part of the paper-and-pencil questionnaires at T0, T1, T2, and T3. To assess *caregiving burden*, caregivers will complete the German short version of the Home Care Scale (10 items, 0 = “exactly correct” to 3 = “not correct”; [39]). To assess *positive aspects of caregiving*, caregivers complete a German version of the Positive Aspects of Care Questionnaire (6 items; 0 = “strongly disagree” to 4 = “strongly agree”; [40]). The German version of the questionnaire is currently being validated. To assess caregivers’ *caregiving self-efficacy*, caregivers will complete the Satisfaction with One's Own Performance as a Caregiver subscale of the abbreviated Sense of Competence Questionnaire (5 items, 0 = “does not apply” to 5 = “applies”; [41]).

#### Immediate reactions to individualized music listening

Directly before and after IML, participants with dementia in the IG group will use the Smiley Assessment Scale (SAS) to assess their *current mood* via the app. Participants with dementia select which of three faces (happy, neutral, unhappy) best depict their mood (adapted from Rosenberg and Mittelman & Epstein [42, 43]).

Directly before and after IML, caregivers in the IG group will use visual analogue scales ranging from 0 to 100 [34] to assess the person with dementia’s *emotional well-being* and *arousal* via the app. Directly after the listening session, caregivers will additionally use the app to indicate whether the person with dementia displayed each of 19 behaviours (e.g., “singing”, “listening attentively”; yes/no) during the listening session. In addition, caregivers can describe their observations of the person with dementia during the listening session using an open answer format.

During the three home visits, a trained research assistant will use a revised version of the DeCS [17] to assess the behaviour of the person with dementia during the listening session.

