#### Dyadic interaction quality

Caregivers will assess the *dyadic interaction quality* daily via the app and as part of the paper-and-pencil questionnaire at T0, T1, T2, and T3. Caregivers will use a self-constructed questionnaire (8 items, e.g., “We experience moments of joy together”; 0 = “strongly disagree” to 4 = “strongly agree”).

After each home visit, a project member will answer a single item on the dyad’s *global relationship quality* (-2 = “very bad” to + 2 = “very good”). The project member will also complete a self-constructed *relationship quality questionnaire* (16 items; e.g., “They get along well with each other”; -2 = “completely disagree” to + 2 = “completely agree”, or “assessment not possible”).

Trained raters will additionally use videos of the home visits to assess the quality of the dyadic interaction. Three camera recordings are made: frontal view of the person with dementia, frontal view of the caregiver and recording of the overall setting.

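### The 19-item post-session checklist is yes/no with no record of whether the caregiver was present, so a 'no' may mean either 'did not occur' or 'not seen'

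*Protocol article*

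**What the plan says.** Protocol article, Adverse events: "Caregivers should remain present during the first IML sessions to be able to intervene if necessary". No section asks for presence at later sessions.

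Intervention: "The caregiver will be supported to find out what accompaniment the person with dementia needs when listening to the music". Accompaniment is thus left to the individual dyad. The same section says that app guidance covers how to "interact with the person with dementia during the listening sessions", so a caregiver is expected to be there at least some of the time.

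Immediate reactions to individualized music listening: directly after the session, "caregivers will additionally use the app to indicate whether the person with dementia displayed each of 19 behaviours", with the format given as "e.g., “singing”, “listening attentively”; yes/no) during the listening session". Caregivers may add an open-text description. The section does not limit the checklist to sessions the caregiver attended. It also provides for independent observation: "During the three home visits, a trained research assistant will use a revised version of the DeCS".

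Two other instruments do have a non-assessable answer: the Cornell scale ("3 = “assessment not possible") and the project member's relationship questionnaire ("or “assessment not possible").

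Intervention experiences, fidelity and acceptance lists what the app logs: how often and how long music is played, pauses, endings and skipped songs. Caregiver presence is not on the list.

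**The concern.** Whether someone listened attentively has to be watched. A caregiver who was out of the room and is offered only yes or no has no described way to report that the behaviour was not observed. Unattended sessions are a foreseeable use of the app: the Background cites a break for the caregiver as a benefit found in earlier home-based work.

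Reactions to the music are named in the Abstract as a secondary outcome. What is at stake is whether the checklist can be read as a rate of reactions and, above all, as a course over six weeks. Because presence is requested specifically at the start, attendance may well fall later, and a fall in attendance could be mistaken for a fading response.

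The planned analysis would not reveal this. Statistical analysis relies on full maximum likelihood and on sensitivity analyses for missing data. An answer entered for an unobserved behaviour is not missing, so neither method detects it.

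**Working it through.** The protocol states no figure for this point, so there is none to reproduce. The check has two parts.

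**1. What the described data can distinguish**

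| Question | Described in the protocol? |
|---|---|
| Presence requested at first sessions | Yes (Adverse events) |
| Presence requested at later sessions | No; accompaniment varies by dyad (Intervention) |
| Checklist limited to attended sessions | No (Immediate reactions) |
| 'Not observed' answer on the checklist | No; yes/no only |
| Presence logged by the app | Not among the listed items (Intervention experiences) |
| How an unattended session is coded | Not stated |

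The trained observer attends three home visits. Planned sessions number 42 days / 2 = 21, which agrees with the 21 in Statistical analysis. With one observed session per visit, independent observation covers 3/21 = 14% of planned sessions.

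**2. How large the effect could be**

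All inputs here are assumptions: p is the true rate of a behaviour, the same at attended and unattended sessions, and u is the share of sessions unattended. Attended sessions are taken to be scored correctly.

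- Unattended items answered 'no': recorded rate = p(1 − u).
- Unattended items left blank: recorded rate = p.
- Unattended items all guessed 'yes' (the opposite extreme): recorded rate = p(1 − u) + u.

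With p = 0.60:

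| Attended (1 − u) | All 'no' | Blank | All 'yes' |
|---|---|---|---|
| 100% | 0.60 | 0.60 | 0.60 |
| 80% | 0.60 × 0.80 = 0.48 | 0.60 | 0.48 + 0.20 = 0.68 |
| 50% | 0.60 × 0.50 = 0.30 | 0.60 | 0.30 + 0.50 = 0.80 |
| 30% | 0.60 × 0.30 = 0.18 | 0.60 | 0.18 + 0.70 = 0.88 |

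For other true rates under 'no' coding, with u running from 0 to 0.75, p = 0.30 is recorded between 0.30 and 0.30 × 0.25 = 0.075, and p = 0.90 between 0.90 and 0.90 × 0.25 = 0.225.

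The apparent habituation is the 'no' column read downwards: full attendance in week 1 and 50% in week 6 would show a fall from 60% to 30% with no real change. It needs both falling attendance and 'no' coding. With full attendance, or with blanks, there is no dilution.

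**The case against.** A reader might infer that caregivers must complete the form after every session and that unattended sessions are stored as 'no reaction'. The documents do not support that. Nothing says the form is compulsory or that blanks become 'no'; a caregiver could skip it, leave items blank, guess, or use the open-text field. The direction of any error is therefore not fixed.

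Nor does the protocol say that caregivers leave after the first sessions. The presence sentence is a safety recommendation, and the guidance on interacting, lowering the volume or changing the song presupposes someone at hand. Unattended sessions could be rare.

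It is also tempting to say that negative reactions go unrecorded and tolerability is understated. The two example behaviours are neutral or positive, and nothing shown establishes that the 19 items include negative ones. Pauses, endings and skipped songs are logged regardless of presence.

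The reach is narrow. Only the intervention group completes the checklist, and no time-trend analysis of it is specified. Smiley self-ratings, caregiver analogue scales and the observer's coding also describe reactions. Finally, skip logic may be described in the full protocol or additional file 1, neither of which is shown; and the 23-item dichotomous behavioural scale also lists no non-assessable answer.

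Most of this stands, and it limits the claim. It does not remove the ambiguity. The article gives response formats in detail and names a non-assessable answer for two other instruments, but only yes/no for the form whose rater may have been out of the room. The smileys and analogue scales measure mood and arousal before and after, not behaviour during listening, and the observer sees few of the sessions.

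**Conclusion.** The concern holds in a limited form. As described, the checklist is not tied to caregiver presence and offers no way to say that a behaviour was not seen, so 'no' may mix two meanings that cannot be separated later from the data listed.

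The size is unknown. The dilution from 60% to 48%, 30% or 18% is conditional on assumed attendance, an assumed true rate and 'no' coding, none of which the protocol states; it is zero if attendance is complete or unobserved items are left blank.

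The consequence is confined to the description of reactions to music within the intervention group. A reader might infer that the trial's effect estimates are distorted; they are not by this route. Goal attainment does not use the checklist, and there is no control-group counterpart to compare. This is an inexpensive improvement to one secondary measure.

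**What to change.** In the post-session app form:

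- add one item on caregiver presence (throughout / partly / not);
- add a 'not observed' answer to each of the 19 behaviours.

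In the analysis, compute behaviour rates over observed sessions, report the share of sessions observed by week beside them, and read any time course against that share. State that attended sessions may be a selected subset, since caregivers may stay when more accompaniment is needed; observed-only rates remove the dilution but not this selection. If the app already lets caregivers skip the form or leave items blank, the plan should say so and say how these are coded.

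The cost is a small app update and a few seconds per session. Sessions recorded before the update lack the presence flag and should be identified as such. The item records presence and does not change who should be present.

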#### Dyadic interaction quality

Caregivers will assess the *dyadic interaction quality* daily via the app and as part of the paper-and-pencil questionnaire at T0, T1, T2, and T3. Caregivers will use a self-constructed questionnaire (8 items, e.g., “We experience moments of joy together”; 0 = “strongly disagree” to 4 = “strongly agree”).

After each home visit, a project member will answer a single item on the dyad’s *global relationship quality* (-2 = “very bad” to + 2 = “very good”). The project member will also complete a self-constructed *relationship quality questionnaire* (16 items; e.g., “They get along well with each other”; -2 = “completely disagree” to + 2 = “completely agree”, or “assessment not possible”).

Trained raters will additionally use videos of the home visits to assess the quality of the dyadic interaction. Three camera recordings are made: frontal view of the person with dementia, frontal view of the caregiver and recording of the overall setting.

#### Acute and chronic physiological stress

We will use videos of the home visits and FaceReader software (Noldus) to assess the *heart rate variability* of the person with dementia and the caregiver as an indicator of acute physiological stress before, during, and shortly after IML (immediate and short-term effects) [26, 44]. FaceReader uses photoplethysmography to detect heart rate in video recordings of faces [45]. We will use the *cortisol/dehydroepiandrosterone concentrations* in the hair samples collected in the first and third home visits as an indicator of chronic physiological stress before and after six weeks of IML (i.e., longer-term effects) [26, 46].

